**Inclusion criteria**
Minimally 1 or 2 radiographically identifiable infrabony defects, with a clinical attachment loss and probing pocket depth of ≥5 mm after initial therapyDepth of intraosseous component of the defect ≥3 mmThe radiological base should be ≥3 mm coronal to the tooth’s apexThe test teeth must have at least 3 mm of keratinized gingiva
**Exclusion criteria**
Presence of stage 4 grade C periodontitisPatients with poor oral hygiene (plaque index>1)Habit of smokingStudy tooth with mobility exceeding grade 2 and exhibiting a class 3 or class 4 furcation defectHistory of periodontal surgical therapy of the selected quadrantWomen who are pregnant or lactatingNote: The inclusion and exclusion criteria are based on the American Academy of Periodontology 2017 classification [1].

### Intervention Description

Before the surgical procedure, patients will be instructed to rinse their mouths for 1 minute with 0.2% chlorhexidine gluconate solution. Only the oral cavity will be visible because of the patient’s drapes. The patient will remain aseptic for the duration of the process. Using a local anesthetic solution of 2% lidocaine containing 1:100,000 epinephrine (Ligno-Ad local anesthetic, Proxim Remedies), the surgical site will be anesthetized by a nerve block or infiltration anesthesia.

#### Flap Design (Incisions)

A conventional approach consisting of a periodontal access flap will be initiated by intracrevicular (sulcular) incisions using Bard-Parker number 12 or 15 surgical blades on the buccal and lingual aspects. The incisions will be carried as far interproximally as possible to preserve the entire interdental papillae to achieve primary wound closure. A tooth mesial and distal to the defect-associated tooth will be included in the flap. If necessary, divergent vertical relieving incisions will be made one tooth away from the defect, where further access will be required.

#### Flap Reflection

A full-thickness mucoperiosteal flap will be reflected using a periosteal elevator (24G Hu-Friedy) to expose the alveolar bone in the area of the osseous defect. Extreme care will be taken to avoid flap perforation or loss of papillae during removal of granulomatous tissue from the inner aspect of the flap.

#### Debridement and Root Surface Management

The osseous defect will be debrided off the granulation tissue using hand instruments (Gracey curettes, Hu-Friedy) followed by ultrasonic instruments (EMS, Minipiezon), thus exposing the root surface, alveolar bone, and periodontal ligament. Any granulomatous tissue or epithelium adherent to the inner surface of the flap or papillae will be judiciously removed, taking care not to overthin the flap. The root surfaces will be planned to remove plaque and calculus by using ultrasonic instruments, followed by hand instrumentation. The root surfaces will be planed until a smooth and hard consistency is obtained.

At this stage, direct measurements of the vertical bone defects (BDs) and the number of bony walls present will be recorded with the UNC-15 probe. If the BD depth is ≥3 mm vertically, final participant eligibility will be confirmed.

#### Preparation of Autologous PRF

As part of the protocol, approximately 6 mL to 10 mL of venous blood will be collected from the patient’s forearm using an 18G needle in a sterile plastic vacutainer for the preparation of autologous PRF by venipuncture of the median cubital vein and transferred to fresh sterile test tubes and without adding any anticoagulant, the original amount of blood will be divided equally in 2 tubes, which will be placed symmetrically around the rotor axis for proper balancing and centrifuged at 3000 rpm for 10 minutes to produce autologous PRF.

#### Preparation of ASB

Following complete debridement, an 18G needle will be used to draw about 30 mL of venous blood from the patient’s forearm using 1 of 2 vacutainer types: (1) noncoated for autologous fibrin glue and (2) glass coated for concentrated growth factor (CGF) and alternated controlled centrifugation at 2400 rpm to 2700 rpm will be performed for 12 minutes. The autologous fibrin glue obtained will then be mixed with OCP-DBBM for polymerization, which produces a yellow, sticky bone. CGF will be mixed with the prepared sticky bone to produce the CGF–sticky bone mixture.

#### Procedure for Group 1

Complete isolation and hemostasis of the defect will be achieved. The flap will be presutured without tying the knot to allow rapid flap closure after placement of graft material. ASB will be placed into the osseous defect at the test site with light pressure until it is filled to the most coronal level of the osseous wall by raising the flap. The flap will then be coronally repositioned and sutured in such a way that the flap margin will be located 1 mm to 2 mm coronal to the cemento-enamel junction (CEJ), ensuring primary flap closure. A combination of vertical mattress and interproximal sutures (4-0 nonresorbable surgical sutures, braided black silk [Mersilk, Ethicon; Johnson & Johnson Ltd]) will be used to secure the flap in position. Slight pressure will be applied to the area with saline-soaked gauze for approximately 2 minutes to adapt the soft tissue well to the tooth surface and eliminate any space in which a clot might form and disrupt reattachment. The surgical site will be dressed with a periodontal dressing (Coe-Pak, GC Inc) on the buccal and lingual aspects.

#### Procedure for Group 2

The surgical procedure for the defect site will be identical to the procedure of the test site, except that osseous defects at group 2 sites will be packed with OCP-DBBM, and then a PRF membrane will be placed over the bone graft.

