Both osteoconductive and osteoinductive qualities are present in the new gold standard for xenografts, macropore octacalcium phosphate–coated deproteinized bovine bone.

This is made from a 100% bovine cancellous bone substitute. Because graft bone materials have a high osteoconductivity, they aid in the proliferation of osteogenic cells and microvessels, which in turn stimulate the formation of new bone [8].

To facilitate the successful regeneration of damaged periodontal tissues, autologous sticky bone (ASB) was introduced as an alternative. ASB is defined as a physiologically solidified bone graft that is embedded in the fibrin network. Strong interconnection of particle bone powders by the fibrin network prevents scattering, even when shaken with a cotton plier. Sticky bone offers many benefits: (1) it can be shaped to suit virtually any kind of bony defects; (2) it prevents the grafted bone from moving; (3) no biochemical additives are needed to maintain the volume of augmentation during the healing period, thereby minimizing the need for block bone and titanium mesh; (4) fibrin accelerates bone and soft tissue regeneration by entrapping platelets and leukocytes that release growth factors; and (5) fibrin interconnection minimizes soft tissue ingrowth into the sticky bone graft [9].

One of the newest developments in regenerative surgery is the use of platelet concentrates for in vivo tissue engineering applications: the first two are platelet-rich fibrin (PRF) and platelet-rich plasma. Platelet concentrates, a concentrated solution of growth factors produced from platelets, are applied as a bioactive surgical adjuvant to facilitate the healing of wounds [10].

As radiographs can identify the quantity and type of damage to the alveolar bone, they play a significant role in periodontal diagnostics. Further research comparing radiographs to presurgical measures found that “bone loss can be underestimated by 1.5 mm, with considerable differences in examiners’ interpretations” [11].

Computed tomography scans have been explored for their potential in highly accurate 3D image alignment. However, they have limitations, including significant radiation exposure and the bulkiness and expense of the equipment [12]. Cone-beam computed tomography (CBCT) has recently emerged as a viable technique in dentistry, offering a lower-cost alternative to traditional computed tomography while still producing high-quality pictures and exposing patients to less radiation.

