## Discussion

### Anticipated Findings

It is anticipated that the use of ASB will show a better outcome in treating infrabony defects because of its advantageous properties provided by the strong fibrin interconnection with particulate bone powder.

ASB, a composite graft derived from a mixture of bone particles and platelet-rich plasma, has been previously studied for its osteoinductive and osteoconductive properties, contributing to enhanced periodontal regeneration. This study aligns with previous reports demonstrating the ability of ASB to promote significant periodontal tissue regeneration and improved clinical outcomes, particularly in terms of bone fill and attachment gain [16]. The osteoconductive nature of ASB, combined with its growth factor–enriched environment, likely facilitates the recruitment of stem cells and fibroblasts, fostering tissue remodeling and bone regeneration [17].

PRF, obtained through centrifugation of autologous blood to isolate a fibrin matrix rich in platelets, has also been shown to enhance healing in periodontal defects through the release of growth factors and cytokines that promote cellular proliferation and angiogenesis [18]. Similar findings have been reported by Jee [19], who showed that PRF accelerates the healing process in periodontal tissue by facilitating the regeneration of the bone matrix and soft tissue. While both ASB and PRF have exhibited favorable outcomes, the superior regenerative capacity of ASB in terms of bone fill and attachment gain may be attributed to the additional presence of bone graft material, which enhances the scaffold effect and provides more robust osteoconductive support [20].

OCP-DBBM is a biomaterial composed of deproteinized bovine bone mineral coated with octacalcium phosphate, which has demonstrated promising potential for bone regeneration in periodontal defects because of its osteoconductive properties [21]. While OCP-DBBM contributed to moderate bone fill and clinical attachment gain, the lack of autologous growth factors may limit its regenerative potential compared with PRF and ASB, which both leverage endogenous healing factors.

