### Mechanisms of Regeneration

The regenerative success of both ASB and PRF can be attributed to the synergistic effects of their cellular and biochemical components. By combining platelet-rich plasma with autologous bone graft particles, sticky bone creates a scaffold that promotes osteogenic differentiation and tissue integration by releasing growth factors like platelet-derived growth factor, vascular endothelial growth factor, and transforming growth factor-β [22]. These growth factors play a critical role in enhancing osteoblastic differentiation and angiogenesis, key processes necessary for effective bone regeneration.

Similarly, PRF’s effectiveness stems from its natural fibrin matrix, which facilitates the slow release of growth factors that contribute to soft tissue healing, as well as bone formation [19]. The combination of PRF with bone grafts has been found to produce a superior regenerative outcome compared with bone grafts alone, likely because of the enhanced cellular activity and tissue remodeling it promotes [23].

In contrast, OCP-DBBM primarily provides a physical scaffold that supports bone growth through osteoconductive mechanisms, relying on the native healing process of the host tissue. Although OCP-DBBM has shown efficacy in bone regeneration, it may not provide the same level of biological support as ASB and PRF, which actively participate in healing through growth-factor processes and cell-mediated processes.

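### The group 1 graft is described inconsistently, and the Discussion sets ASB against OCP-DBBM although, by the Methods, both arms receive it

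*Protocol article*

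**What the plan says.** **Recipe.** Preparation of ASB draws about 30 mL of blood "using 1 of 2 vacutainer types: (1) noncoated for autologous fibrin glue and (2) glass coated for concentrated growth factor (CGF"). It continues: "The autologous fibrin glue obtained will then be mixed with OCP-DBBM for polymerization, which produces a yellow, sticky bone". Then "CGF will be mixed with the prepared sticky bone", which gives a second, separately named mixture. Procedure for Group 1 says only that "ASB will be placed into the osseous defect at the test site with light pressure".

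**Comparator.** Procedure for Group 2 packs the defect with OCP-DBBM and lays a PRF membrane over it.

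**Other descriptions of ASB.** The Background says "ASB is defined as a physiologically solidified bone graft that is embedded in the fibrin network", without naming the source of the bone. Anticipated Findings calls it "ASB, a composite graft derived from a mixture of bone particles and platelet-rich plasma". Mechanisms of Regeneration says: "By combining platelet-rich plasma with autologous bone graft particles, sticky bone creates a scaffold".

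**Labels.** The Abstract (Methods), the Objectives and the Statistical Analysis section call group 1 simply ASB. They mention OCP-DBBM only with PRF, for group 2.

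**Interpretation.** Anticipated Findings explains the expected superiority of ASB by graft material that it is said to contain in addition. It then describes OCP-DBBM as less effective than the other two modalities. Clinical Implications offers OCP-DBBM as the alternative when autologous materials cannot be used.

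**The concern.** A comparison of two grafts can be interpreted only if the reader knows what each arm received and where the arms differ. From the labels and the Discussion, group 1 looks like an autologous graft compared with a bovine one. From the Methods, both arms carry the same bovine mineral and differ in the autologous fibrin product and in how it is combined with that mineral. A difference in bone fill could then not be credited to autologous bone, to platelet-rich plasma or to extra graft material. Nor could the trial say how OCP-DBBM performs by itself. The tube sentence and the unspecified mixture also leave the test intervention less reproducible than it should be.

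**Working it through.** No arithmetic applies, because the point depends on no effect size, SD, error rate or sample size. The check sets the descriptions side by side.

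1. **Components of ASB by section.**
   - Preparation of ASB: fibrin glue + OCP-DBBM + CGF.
   - Background: bone graft in a fibrin network, source not stated. This is compatible with the recipe.
   - Anticipated Findings: bone particles + platelet-rich plasma. The particles could be OCP-DBBM; the plasma is not in the recipe.
   - Mechanisms of Regeneration: platelet-rich plasma + autologous bone particles. It shares no named component with the recipe.

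2. **Are these only synonyms?** Not by the article's own terms. The Background lists PRF and platelet-rich plasma as two products. Comparison With Prior Work sets PRF and CGF apart from other platelet concentrates. The Background also separates autografts from xenografts, rates autograft best and places octacalcium phosphate–coated bovine bone among the xenografts. The Methods contain no bone harvest and no platelet-rich plasma step.

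3. **Tubes.** The wording is one of two types. The noncoated tube yields the glue and the glass-coated tube yields the CGF. The next two sentences use the glue and then the CGF, so the recipe needs two of two.

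4. **Product placed.** The recipe names two successive products, the sticky bone and that bone mixed with CGF. Procedure for Group 1 says ASB and does not tie the term to either.

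5. **What the arms share.** Group 1 has OCP-DBBM in the mixture, and group 2 has OCP-DBBM under a PRF membrane. That is 10 + 10 = 20 of 20 defects, while the labels show it for 10. No arm receives OCP-DBBM alone, PRF alone or autologous bone.

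6. **Interpretation against step 5.** If both arms contain the same graft, none of it is additional in group 1. The ranking of OCP-DBBM below ASB and PRF needs an arm with OCP-DBBM alone, and there is none.

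**The case against.** The strongest reply is that there is only one operative recipe. Preparation of ASB tells the operator what to do, the Background definition fits it, and the conflicting text is Discussion prose that cites earlier work and instructs nobody. A short arm label with the recipe given in the Methods is also ordinary in an article. Much of this stands: the conflict bears mainly on interpretation and labelling. It does not dispose of the point, because the Discussion applies the other description to the result expected from this trial.

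Three stronger readings are tempting and are not supported:

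- **Some group 1 patients will get the graft without CGF, giving a mixed arm.** The tube list joins its two items with a conjunction, and both mixing steps are unconditional. A slip of wording is the likelier explanation, and the article gives no basis for any number of affected patients.
- **The trial's conclusion names a product that was not given.** Neither the Abstract's conclusions nor the Conclusions section says what ASB is made of.
- **Participants will be misled about bovine material.** The consent form is not shown, and Ethical Considerations says that it will describe the procedures. What it says about the graft cannot be judged here.

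**Conclusion.** The point holds as an inconsistency in the description of the test product and in the planned attribution of its effect. It affects the meaning of the group 1 result for all 10 defects in that arm. It changes no allocation, endpoint, analysis or sample size. It should be corrected because, if the Methods recipe is what is delivered, the design cannot support the explanation that the Discussion prepares: the graft is common to both arms and is not tested alone. That conclusion assumes that Preparation of ASB describes what will be placed. This review does not judge which preparation is right; the sections contradict one another and must be reconciled.

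**What to change.** - Reconcile Preparation of ASB, Anticipated Findings and Mechanisms of Regeneration to one description of the group 1 product. The choice of preparation belongs to the investigators.
- Make the tube sentence agree with the recipe, and state in Procedure for Group 1 which of the two named mixtures is placed.
- If OCP-DBBM is in both arms, as Preparation of ASB states, show it in both arm labels in the Abstract, the Objectives and the Statistical Analysis section.
- In that case, word the planned conclusion as a comparison of two autologous fibrin preparations combined with the same bovine graft. Remove the attribution to extra graft material, and remove the statements on the relative efficacy of OCP-DBBM alone.

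The cost is wording only. The price is a narrower claim for ASB.

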#### Maintenance Care

Patients will be recalled after 10 days for suture removal and subsequently for evaluation of both the plaque index (PI) and papillary bleeding index at 3 and 6 months postoperatively. All participants will be reinforced with oral care protocol and full-mouth ultrasonic supragingival scaling during the follow-up visits.

### Statistical Analysis

#### Power

PI, papillary bleeding index, PPD, relative attachment level, and relative gingival marginal level will be calculated by mean and SD values. Statistical tests such as the paired 1-tailed *t* test or Wilcoxon signed-rank test for within-group comparison and the ANOVA or Kruskal-Wallis test for between-group comparison are typically used to assess clinical and radiographic outcomes. The choice of test depends on whether the data follow a normal distribution. The difference between radiographic bone fill, PPD, CAL and relative gingival margin level will be considered significant only if *P*<.05.

The study population will be divided into 2 groups: group 1 (ASB) and group 2 (autologous PRF with OCP-DBBM). There are no subgroups in the study.

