### Probing Measurements

Both treatment groups will be subjected to recordings to measure PPD, relative CAL, and relative gingival margin level at 6 sites of the selected teeth. Measurements will be carried out using a UNC-15 calibrated periodontal probe (University of North Carolina) at the mesiobuccal, mesiolingual, distobuccal, distolingual, midbuccal, and midlingual points of the selected tooth. After measurement, only the deepest marking per defect will be considered for study purposes. After the fabrication of the acrylic stent, probing measurements will be recorded at baseline and 6 months postoperatively.

The UNC-15 probe will be positioned on the prepared groove of the acrylic stent. The probe will be placed with its tip at the gingival marginal level, and the distance between the gingival margin and the lower border of the stent will be measured as the relative gingival margin level. Then, the probe will be positioned at the bottom of the pocket, and the distance from the lower border of the stent to the bottom of the pocket will be noted as the relative CAL. PPD will be measured by subtracting the relative gingival margin level from the relative CAL. The width of keratinized gingiva will be calculated from the lowest point of the mucogingival junction to the crest of the gingival margin using the UNC-15 probe.

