### Secondary Outcomes

In addition to the primary outcome, the study also assesses secondary outcomes, which include the following:

CAL gain, which measures the improvement in the attachment of the periodontal tissue to the tooth, indicating successful regeneration.PPD reduction, which is used to evaluate the decrease in the depth of periodontal pockets, which is a sign of improved periodontal health.Relative gingival marginal level, which has been documented to assess the health of the gingival tissue surrounding the teeth.

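### Relative gingival margin level is carried as a stent-referenced level, so its between-group comparison can pick up stent height; the plan should name change or a baseline-adjusted value

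*Protocol article*

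**What the plan says.** Under Probing Measurements, two readings are taken from the stent. For the margin, "the distance between the gingival margin and the lower border of the stent will be measured as the relative gingival margin level". For attachment, "the distance from the lower border of the stent to the bottom of the pocket will be noted as the relative CAL". Pocket depth follows by difference: "PPD will be measured by subtracting the relative gingival margin level from the relative CAL". On timing, "After the fabrication of the acrylic stent, probing measurements will be recorded at baseline and 6 months postoperatively".

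The Power paragraph of the Statistical Analysis section lists the measures descriptively: "PI, papillary bleeding index, PPD, relative attachment level, and relative gingival marginal level will be calculated by mean and SD values". It names a one-tailed paired t test or the Wilcoxon signed-rank test within groups. Between groups, "the ANOVA or Kruskal-Wallis test for between-group comparison are typically used to assess clinical and radiographic outcomes". The significance rule begins "The difference between radiographic bone fill, PPD, CAL and relative gingival margin level will be considered significant only if" and sets P<.05.

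Secondary Outcomes lists CAL gain, PPD reduction and, third, relative "gingival marginal level, which has been documented to assess the health of the gingival tissue surrounding the teeth". The first two are changes. The third is a level.

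The abstract (Objective and Conclusions) and the Objectives section also describe attachment as a gain or an increase.

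**The concern.** The lower border of a stent is set when the stent is made; it is not an anatomical landmark. The article does not say that each patient has their own stent. A stent with a prepared groove on selected teeth presumably does belong to one patient, and I assume so here. Two patients with the same gingival margin position can then have different relative margin levels because their stents end at different heights.

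The offset cancels in three places: in PPD, which subtracts one stent reading from the other; in a paired within-group test; and in any change from baseline read with the same stent. It does not cancel in a between-group comparison of 6-month levels. If the text is followed as written for relative gingival margin level, the comparison contains stent height as noise, and a group mean in millimetres has no anatomical meaning.

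A second, smaller matter concerns attachment. By the article's own definition, a larger relative CAL means a deeper pocket base, that is, attachment loss. The objectives call the desired result an increase, and the within-group t test is one-tailed. The sign therefore has to be fixed, and it is not.

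**Working it through.** **What the article supplies.** It gives 10 per group, and baseline and 6-month readings from the stent. It gives no SD, correlation or target difference for either relative level, so there is no figure of the plan's own to reproduce on this point. The 10 per group is taken as given.

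**Assumptions.**
- *b* is the SD of true margin position between patients, 1.0 to 1.5 mm.
- *S* is the SD of stent-border height between patients, 0.5 to 3 mm, independent of position.
- *ρ* is the correlation of true position between baseline and 6 months, 0.3 to 0.7.
- The true difference between groups is 1 mm; the test is two-sided at 5%.

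**Formulas.**
- Level at 6 months: variance = b² + S².
- Change from baseline, same stent: variance = 2b²(1 − ρ). *S* drops out.
- Power: noncentral t with 18 degrees of freedom and noncentrality 1/(SD × √(2/10)).
- 95% CI half-width: 2.101 × SD × √(2/10).

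**Central case, b = 1.0 mm and ρ = 0.5.** The variance of change is 2 × 1 × 0.5 = 1.0.

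| Quantity compared | SD (mm) | Variance relative to change | CI half-width (mm) | Power |
|---|---|---|---|---|
| Change | 1.00 | 1.00 | 0.94 | 56% |
| Level, S = 0.5 | 1.12 | 1.25 | 1.05 | 47% |
| Level, S = 1 | 1.41 | 2.0 | 1.33 | 32% |
| Level, S = 2 | 2.24 | 5.0 | 2.10 | 16% |

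The chance difference in mean stent height between the arms has SD S × √(2/10): 0.45 mm for S = 1 and 0.89 mm for S = 2.

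**Range.** Over the full grid of assumptions, the ratio of level variance to change variance runs from 0.79 to 16.7. The level is the more precise of the two when b² + S² < 2b²(1 − ρ), that is, when S² < b²(1 − 2ρ). This cannot happen when ρ is 0.5 or more. At ρ = 0.3 it happens for S below √0.4 = 0.63 mm if b = 1.0 mm, and below √0.9 = 0.95 mm if b = 1.5 mm. At ρ = 0.3 and S = 0.5 mm the ratios are 0.89 (b = 1.0) and 0.79 (b = 1.5).

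**Baseline adjustment.** The correlation between the two stent readings is r = (ρb² + S²)/(b² + S²), and the residual variance after adjustment is (b² + S²)(1 − r²).
- b = 1, ρ = 0.5, S = 1: r = 1.5/2 = 0.75, so 2 × (1 − 0.5625) = 0.875. This compares with 1.0 for change and 2.0 for the level.
- b = 1, ρ = 0.3, S = 0.5, where the level beats change: r = 0.55/1.25 = 0.44, so 1.25 × (1 − 0.1936) = 1.01. This compares with 1.4 for change and 1.25 for the level.

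So, apart from the small cost of estimating one slope, the adjusted value is at least as precise as either alternative in both cases.

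**The case against.** The strongest reply is that the article never says raw levels are tested between groups. The sentence on means and SDs is descriptive, and reporting visit means is routine. The sentence on between-group tests does not say whether the level or the change is analysed, and a derived variable is often fixed in the full protocol or analysis plan, which is not shown. This stands for attachment. A reader might infer that attachment too is compared as a level, but the abstract, the Objectives and Secondary Outcomes all name a gain or an increase, in which the offset cancels if the same stent is used. It does not fully answer the margin outcome: the article names that outcome itself as a level, in the same list as a gain and a reduction, and applies the significance rule to it.

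A reader might also infer that the comparison is biased or must lose much of its precision. Neither is supported. Under randomization, stent height adds noise and chance imbalance, not systematic bias. The precision loss rests on SDs and a correlation that the article does not give, and for some plausible values there is none.

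The reach is also limited. The primary outcome is radiographic and does not use the stent, PPD is unaffected, and the margin level appears neither in the Objectives nor among the abstract's secondary outcomes.

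**Conclusion.** The point holds for one named secondary outcome, relative gingival margin level. It is carried as a quantity with an arbitrary zero, and a between-group test of its raw 6-month value would include stent-height variation. In the central case power falls from 56% to between 47% and 16% as the stent SD goes from 0.5 to 2 mm. These figures are illustrations under stated assumptions, including one stent per patient, and are not properties of the trial. The difficulty in interpreting group means of a stent-referenced level does not depend on them.

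For attachment the defect is narrower: the statistical section lists the relative level without saying that the gain is what is tested, and the sign of the measured variable runs opposite to the stated goal while the within-group t test is one-tailed. Overall this is an inexpensive improvement to the analysis wording and no threat to the primary analysis.

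**What to change.** In the Statistical Analysis and Secondary Outcomes sections:

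1. State that between-group comparisons of relative gingival margin level and relative CAL use the 6-month value adjusted for baseline, or the change from baseline.
2. State that both readings are taken with the same stent at the same groove. Probing Measurements keeps only the deepest reading per defect and does not say that the site is held fixed; if it moves, the offset need not cancel even in a change.
3. Define CAL gain as baseline minus 6-month relative CAL, with positive values meaning improvement, and define the sign of margin change in the same way. Align the one-tailed within-group test with that definition.
4. Keep visit means and SDs as description if wanted, but do not test raw stent-referenced levels between groups.

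The cost is analysis wording only. Both readings are already planned at baseline and 6 months.
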